### Timeline of the study

The schedules of study activities for patients and participating sites are summarized in Tables 1 and 2, respectively. Patient enrollment will commence only after completion of comprehensive guideline-directed medical therapy training for HCPs at both the study-wide and individual site levels. The screening period will extend from 14 days to 1 day prior to enrollment. Following enrollment, patients will receive individualized treatment plans and hyperkalemia management strategies determined by their HCPs, including disease education, self-management materials, prescriptions for RAASi, serum potassium monitoring, and potassium-lowering therapies as appropriate. The maximum duration of follow-up will be 96 weeks. After the baseline visit and initial data collection, each participant will attend six scheduled onsite visits at weeks 12, 24, 36, 48, 72, and 96 post-enrollment. Patients who discontinue participation prematurely will be invited to complete an early withdrawal visit. During intervals without scheduled onsite visits, participants will undergo remote follow-up every 4 weeks. Patients will be considered to have completed the study upon completion of the 96-week follow-up, death, or study termination. The study end date is defined as the date of the final visit of the last enrolled patient.

**Table 1 Tab1:** Schedule of activities for patients

Procedure	Screening period	Management period/follow up^a^							Early Withdrawal + 14 day^c^
Visit ^b^	Day − 14 ~ Day-1	Day 0 Baseline *	Week 12 ± 14 days	Week 24 ± 14 days	Week 36 ± 14 day	Week 48 ± 14 days	Week 72 ± 28 days	Week 96 ± 28 days	
	/	V0	V1	V2	V3	V4	V5	V6	
Informed consent	X								
Inclusion and exclusion criteria	X	X							
Demographics ^d^	X								
Medical history ^e^	X								
Physical examination ^f^	X		X	X	X	X	X	X	
Height, weight	X	X	X (weight only, if available as per clinical practice)						
Laboratory tests (Hematology, Clinical Chemistry, Urinalysis)	X^g^		X	X	X	X	X^h^	X^h^	X^i^
12-lead ECG ^j^	X	X	X	X	X	X	X	X	X
Vital signs ^k^	X	X	X	X	X	X	X	X	
Patient’s daily checklist release and/or retrieve		X	X	X	X	X	X	X	X
RAASi treatment pattern ^l^		X	X	X	X	X	X	X	X
Hyperkalemia treatment pattern ^m^		X	X	X	X	X	X	X	X
Concomitant medication ^n^	X	X	X	X	X	X	X	X	X
Clinical progression/medical events collection			X						X
Administration of study intervention		X	X •Patient education at each onsite visit •Patient self-learning						
AE/SAE^p^	X								X

HCP, health care professional; BP, blood pressure; eGFR, estimated glomerular filtration rate; ECG, electrocardiogram; RAASi, renin-angiotensin-aldosterone system inhibitor; UACR, urinary albumin/creatinine ratio; ESRD, end-stage renal disease; rhHF, rehospitalization for heart failure; HF, heart failure; ER, emergency room; CV-death, cardiovascular death; AE, adverse event; SAE, serious adverse event; ICF, informed consent form; MAH, marketing authorization holder

a. Day 0 refers to the day on which the patient is enrolled

b. Remote visits: Telephone calls will be conducted every 4 weeks (± 7 days) following enrollment if no onsite visit occurs, to review patient self-management and assess adherence. Patients will also be reminded to follow their HCP’s advice regarding serum K⁺ testing, medication adherence, dietary restrictions, etc

c. Early withdrawal visits will be conducted for patients who discontinue early, preferably within two weeks of withdrawal confirmation. These visits may be onsite or remote

d. Demographic data include gender, age, race, and ethnicity

e. Medical history includes comorbidities and relevant conditions requiring medication within 1 year prior to enrollment

f. Physical examination: A complete physical examination will be performed at V0 (Day 0). A brief physical examination will be conducted during follow-up visits. A complete physical examination includes assessment of general appearance; respiratory, cardiovascular, abdominal, skin, head and neck (including ears, eyes, nose, and throat); lymph nodes; thyroid; musculoskeletal (including spine and extremities); and neurological systems. A brief physical examination includes assessment of at least the neurological system, skin, lungs, cardiovascular system, abdomen (liver and spleen), and lymph nodes

g. The serum K⁺ test must be completed within 48 h prior to enrollment. Other laboratory test results within 14 days before baseline may be accepted

h. At weeks 72 and 96, only hematology, urinalysis, renal function (eGFR), blood electrolytes (Na⁺/K⁺/Cl⁻), and UACR will be assessed. Additional laboratory tests may be collected if available per routine clinical practice

i. At early withdrawal visits, only renal function (eGFR) and serum K⁺ will be tested. Additional laboratory assessments may be performed if available per clinical practice

j. Additional ECGs may be performed if available as per clinical practice. ECG results obtained within 14 days prior to baseline may be used as screening data

k. Vital signs include body temperature, systolic and diastolic blood pressure, pulse rate, and respiratory rate

l. RAASi treatment patterns include whether therapy was initiated and, if so, detailed data (drug/treatment name, usage and dosage, frequency, start and end dates, any changes or interruptions, and reasons for discontinuation, if applicable)

m. Hyperkalemia treatment: Pharmacological treatment includes whether therapy was administered and, if so, treatment name, usage and dosage, frequency, start and end dates, and any changes or interruptions with reasons (if applicable). Non-pharmacological treatment includes treatment name, start and end dates, and reason for change or interruption (if applicable)

n. Concomitant medications will be collected throughout the study. Blood pressure and RAASi treatment in the 3 months prior to enrollment will also be recorded. For patients continuing RAASi treatment during screening, the date of the last dose prior to enrollment should be documented

o. Clinical progression/medical events include: Kidney-specific composite events: sustained eGFR decline ≥ 50%, ESRD, or renal-related death. Cardiovascular-specific composite events: rhHF, worsening HF, emergency room visit, or cardiovascular death. Other events: arrhythmia, hospitalization, emergency dialysis, emergency department visit, and death due to other causes

p. Adverse events (AEs): All AEs and SAEs related to potassium binders, as well as special situations (e.g., medication error, drug abuse, misuse, and pregnancy) involving LOKELMA^®^, will be actively collected. The collection period spans from the time of ICF signing (for patients using a potassium binder prior to enrollment) or the date of treatment initiation (for those starting after enrollment) until 24 h post-discontinuation. AEs involving other products for which AstraZeneca is not the marketing authorization holder (MAH) will be reported spontaneously to the respective MAHs

* Demographic and medical history data collected during the screening period may be used as baseline data

**Table 2 Tab2:** Schedule of activities for sites

Procedure	Before first patient is enrolled in the study	Before first patient is enrolled in the site	FPI + 4 weeks	FPI + 12 weeks	FPI + 16 weeks	FPI + 24 weeks	FPI + 28 weeks	FPI + 36 weeks	FPI + 40 weeks	FPI + 48 weeks	FPI + 96 weeks
GDMT comprehensive training	X LPI to site investigator	X Site investigator to HCPs									
Mandatory intensive training ^a^			X		X		X		X		
Added intensive training				If off target, ≤ 4 times/site during 0–48 weeks after FPI, totally ≤ 6 times/site, at the individual site level							
Hyperkalemia management status of sites (questionnaire)	X^b^									X^b^	X^b^
Quality audit at the HCP level				X FPI + 3 months		X FPI + 6 months		X FPI + 9 months	X FPI + 12, 15, 18 months		

GDMT, guideline determined medical therapy; PI, principal investigator; HCP, health care professional

a. FPI refers to “first patient in” (unless otherwise specified, at the site level). Mandatory intensive training at the study level (delivered by the leading PI to the site investigator) was conducted at weeks 4, 16, 28, and 40 following first patient enrollment in the study. Mandatory intensive training at the site level (delivered by the site investigator to the site’s HCPs) was conducted at weeks 4, 16, 28, and 40 following first patient enrollment at the individual site

b. A site-level questionnaire assessing hyperkalemia management status was required at baseline and at weeks 48 and 96 after first patient enrollment at each individual site

### Intervention

The study will implement a QIP targeting both HCPs and patients, incorporating standardized hyperkalemia management and ongoing quality audits. The methods and processes of the intervention are outlined in Table 3. Core components of hyperkalemia management include a standardized clinical pathway based on guideline-directed medical therapy, encompassing the use of serum potassium > 5.0 mmol/L as the diagnostic criterion, long-term hyperkalemia management strategies, targeted dosing of RAASi, and protocolized serum potassium monitoring at least every 3 months, or monthly in patients at high risk of hyperkalemia, including those with CKD combined with diabetic kidney disease, CKD combined with heart failure, or CKD undergoing initiation or uptitration of RAASi therapy. Both serum potassium testing frequency and RAASi optimization will be systematically tracked throughout the study. The standardized hyperkalemia management protocol for patients with CKD will be implemented as illustrated in Fig. 2, with the tiered management approach detailed in Table 4. The guideline-directed medical therapy framework is informed by the KDIGO 2024 Clinical Practice Guideline for the Evaluation and Management of Chronic Kidney Disease [17], the Expert consensus on the management of serum potassium in chronic kidney disease patients in China (2020) [18], and the Guidelines for the early evaluation and management of chronic kidney disease in China (2023) [19].

**Table 3 Tab3:** Method and process of intervention

	HCP level	Patient level
Hyperkalemia disease management	Key contents: • Follow clinical pathway: hyperkalemia diagnosis >5.0 mmol/L, hyperkalemia long-term management^#^, RAASi targeted dose treatment and serum K^+^ test at least once per 3 months and high-risk cases^*^ once per month • Track serum K^+^ test frequency and RAASi optimization. Quality audit results as feedback for additional education. Frequency: • 1 comprehensive training • 4 mandatory intensive trainings (every 12w with the 1st at week 4) • ≤6 additional intensive trainings if quality audit is off-target	Key contents: • Disease introduction, poor outcomes and the importance of serum K^+^ monitoring Frequency: • 6 sessions of disease and medication adherence education from HCPs during onsite visits; self-learning
Quality Audit	Evaluate whether HCPs’ perception and action of standardized hyperkalemia management achieve the target. • Questionnaires to survey HCPs’ standardized hyperkalemia management perception • Track serum K^+^ test arrangement to check if arranged	Review patient checklist and self-management to check patient’s adherence and HCP’s clinical behavior

HCP, health care professional

^#^ Hyperkalemia long-term management: Hyperkalemia pharmacological treatment and hyperkalemia non-pharmacological treatment

^*^ High risk hyperkalemia patients: CKD with diabetic kidney disease; CKD with heart failure; CKD on RAASi

**Fig. 2 Fig2:**
[figure not shown]
Guideline-directed management algorithm for hyperkalemia in chronic kidney disease

**Table 4 Tab4:** Actions to manage hyperkalemia in chronic kidney disease

1st line: Correctable factors	• Review non-RAASi medications (e.g., NSAIDs, trimethoprim) • Assess dietary potassium intake (dietary referral) and consider appropriate moderation of dietary potassium intake
2nd line: Medications	Consider: • Appropriate use of diuretics • Optimize serum bicarbonate levels • Licensed potassium exchange agents
3rd line: Last resort	• Reduce dose or discontinue RASi/MRA (Discontinuation is associated with increased cardiovascular events. Review and restart RASi or MRA later if the patient’s condition allows.)

RAASi, renin-angiotensin-aldosterone system inhibitor; NASID, nonsteroidal anti-inflammatory drug; RASi, renin-angiotensin system inhibitor; MRA, mineralocorticoid receptor antagonist

Quality audits will be conducted at both the HCP and patient levels. At the HCP level, audits will be performed quarterly beginning after enrollment of the first patient at each site. Relevant audit data will be regularly extracted and provided as structured feedback to HCPs and site investigators, who will review the findings to promote continuous self-assessment and improvement in care processes. HCPs’ perceptions and implementation of standardized hyperkalemia management will be evaluated quarterly to assess alignment with predefined performance targets. HCP-level quality audits will assess: (1) provision of disease education and self-management materials to patients; (2) prescription practices related to RAASi, serum potassium testing, and potassium-lowering therapies; (3) scheduling of follow-up visits in accordance with the standardized clinical pathway and guideline-directed medical therapy; and (4) administration of questionnaires evaluating HCPs’ perceptions and practices regarding hyperkalemia management. Patient adherence and corresponding HCP clinical behavior will be evaluated through review of patient daily checklists every 12 weeks and self-management reports every 4 weeks. Patient-level quality audits will assess: (1) whether potassium-lowering therapy is prescribed by the designated HCP or self-selected by the patient; (2) whether RAASi therapy is prescribed by the designated HCP or self-selected by the patient; (3) whether serum potassium testing is arranged by the HCP or initiated by the patient; and (4) whether education is received through direct instruction from the designated HCP or via self-learning materials.

Audit results will be used to guide additional targeted medical education, with training serving as a key mechanism to improve hyperkalemia management at both the HCP and patient levels. HCP education focuses on guideline-directed medical therapy and includes instruction on the study design, protocol implementation, core patient management materials (Table S1), and standardized clinical pathway resources (Figure S1). HCP training comprises one comprehensive training session conducted prior to enrollment of the first patient, followed by four mandatory intensive training sessions at weeks 4, 16, 28, and 40, delivered at both the overall study and individual site levels. If quality audit targets are not met, additional site-level intensive training sessions will be implemented, with a maximum of one session per site per quarter during the first 48 weeks after enrollment of the first patient and a total cap of six additional sessions per site. These sessions will be delivered by the site investigator to local HCPs and scheduled between the mandatory intensive training sessions. Details regarding training timelines, formats, and responsible personnel are provided in Fig. 3. Patient education consists of structured disease education and medication adherence instruction delivered by HCPs, supplemented by self-learning materials. At each onsite visit from weeks 12 to 96 (weeks 12, 24, 36, 48, 72, and 96), participating HCPs will reinforce education on disease knowledge, potential adverse outcomes, and the importance of regular serum potassium monitoring. Patients will be supported in recording hyperkalemia self-management information through a dedicated patient-facing mobile application that includes educational push notifications and simplified self-management recording modules; in addition, telephone reminders will be conducted every 4 weeks during remote visits to reinforce healthcare professional guidance on serum potassium testing, medication adherence, and dietary management.

**Fig. 3 Fig3:**
[figure not shown]
Overview of the GDMT training program. PI, principal investigator; HCP, health care professional; GDMT, guideline determined medical therapy

### Assessment and data collection

Demographic data will include age, sex, race, and ethnicity. Medical history will capture comorbid conditions and clinically relevant diagnoses requiring pharmacological treatment within 1 year prior to enrollment. Laboratory assessments will include serum potassium, UACR, and eGFR, with UACR calculated from measured urinary albumin and creatinine concentrations.

Patterns of RAASi use will be documented, including whether therapy was initiated or continued and, where applicable, the specific drug name, dosage, frequency, start and end dates, and any dose modifications or interruptions, together with the underlying reasons. Pharmacological treatments for hyperkalemia will be recorded in a similar manner, including treatment details and reasons for discontinuation or interruption. Non-pharmacological hyperkalemia management strategies will also be documented, including the intervention type, start and end dates, and reasons for any changes or discontinuation. Clinical progression and medical events will include kidney-specific composite outcomes (sustained eGFR decline ≥ 50%, ESRD, or renal-related death), cardiovascular-specific composite outcomes (rhHF, heart failure-related emergency visits, or cardiovascular death), as well as arrhythmias, hospitalizations, emergency dialysis visits, and death from other causes. In addition, the hyperkalemia management status of each participating site will be assessed using a site-level questionnaire administered at baseline and at weeks 48 and 96 following enrollment of the first patient (Table 2).

Safety will be monitored throughout the study period. A comprehensive baseline assessment will be conducted for each participant, including demographic characteristics, medical history, electrocardiograms, laboratory parameters, vital signs, height, weight, and physical examination findings. During the study, vital signs, electrocardiograms, and laboratory assessments will be performed according to the schedule specified in Table 1. AEs, SAEs, and concomitant medication use will be continuously monitored and systematically recorded. Each reported SAE will be individually reviewed to assess its potential impact on participant safety and the overall conduct of the study. Cumulative AEs will be tracked throughout the study, and all AEs will be followed until resolution, stabilization, or completion of the end-of-study visit.

### Sample size estimation

The study is expected to enroll approximately 1,000 patients, based on the estimated eligible patient population across China and the participation of approximately 50 research centers over an anticipated enrollment period of 10 months. As this study is descriptive in nature, the sample size was determined to ensure adequate precision of estimates rather than formal hypothesis testing. Assuming that 45% of patients will achieve RAASi optimization while maintaining normokalemia (serum potassium 3.5-5.0 mmol/L) at 48 weeks [20], and allowing for an anticipated 20% dropout rate, a total sample size of 1,000 patients is expected to provide a precision of 3.4% for the primary endpoint, calculated using the normal approximation method.

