### Statistical plans

All statistical analyses will be performed using SAS software (version 9.4 or later). Analyses will be primarily descriptive in nature and will be conducted using non-missing data only.

Except for safety analyses, all efficacy and exploratory analyses will be performed in the full analysis set (FAS), which includes all patients who meet the inclusion and exclusion criteria, unless otherwise specified. Continuous variables will be summarized using the number of observations, mean, standard deviation, median, first and third quartiles, minimum, and maximum. Categorical variables will be summarized as frequencies and percentages. 95% confidence intervals (CIs) will be reported where appropriate. For time-to-event endpoints, analyses will include the number and proportion of patients experiencing each event, along with the corresponding event rates. Kaplan-Meier methods will be used to estimate and graphically present cumulative incidence for both composite and individual endpoints. Changes in eGFR over time will be evaluated using a mixed-effects model for repeated measures (MMRM) to estimate the eGFR slope over the study period.

Safety analyses will be conducted in the safety analysis set (SAS), which includes all patients who have received at least one potassium-binding therapy. The number and proportion of patients experiencing at least one AE, SAE, or ADR will be summarized. Vital signs at each scheduled assessment, as well as findings from physical examinations, electrocardiograms, and laboratory evaluations, will be summarized using descriptive statistics.

A total of four interim analyses are planned, including one primary analysis. The primary analysis is scheduled to occur 48 weeks after enrollment of the final patient.

In addition, predefined subgroup analyses will be performed for the primary and selected secondary endpoints. Subgroups will be defined based on demographic characteristics, baseline disease features (including baseline eGFR to reflect CKD stage), geographic region, and other clinically relevant factors such as history of heart failure, diabetes mellitus, RAASi use, and hyperkalemia treatment patterns.

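### The stated 3.4% precision assumes 800 independent patients and makes no allowance for about 50 sites, although the programme is delivered and audited site by site

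*Protocol article*

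**What the plan says.** The section Sample size estimation gives two grounds for the number of patients. The first is feasibility: "The study is expected to enroll approximately 1,000 patients", in view of the eligible population, a 10-month enrolment period and "the participation of approximately 50 research centers". The second is precision, since the study is described as descriptive and tests no hypothesis. The precision inputs are "Assuming that 45% of patients will achieve RAASi optimization while maintaining normokalemia" at 48 weeks and "allowing for an anticipated 20% dropout rate". The result is that "a total sample size of 1,000 patients is expected to provide a precision of 3.4% for the primary endpoint", "calculated using the normal approximation method". The centres enter that paragraph only as a source of recruitment. No ICC, design effect or site-size assumption is given.

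The section Statistical plans says that analyses use non-missing data and that "95% confidence intervals (CIs) will be reported where appropriate". It names no interval method for the primary endpoint, and it neither includes nor excludes an adjustment for site.

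The section Intervention and Table 2 describe a programme that works through the hospital. Staff audits run quarterly from the first patient at each site, and results are fed back to that site. Extra training, up to six sessions per site, is triggered by the site's own audit result. Of these extra sessions the article says: "These sessions will be delivered by the site investigator to local HCPs".

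**The concern.** The binomial half-width is valid if patients' outcomes are independent. Here the treating staff are trained, audited and retrained as a site team, and the intensity of the programme differs between sites. One half of the primary endpoint, RAASi optimisation, is largely a prescribing decision, and the Background itself points to variation in how clinicians treat. Secondary endpoint 7 measures the hospital's own management status, so the document already treats the hospital as a unit that can differ and change. Positive correlation within sites is therefore plausible.

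Two things are at stake. The 3.4% is the only statistical justification offered for the sample size, and positive correlation makes it too favourable. In a single-arm descriptive study the main result is an estimate with its interval, so an interval that ignored site would overstate how well the success proportion is known.

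**Working it through.** **Inputs from Sample size estimation**
- Assumed proportion p = 0.45.
- Enrolled 1,000, dropout 20%, so evaluable n = 1,000 × 0.80 = 800. This fits the non-missing-data rule in Statistical plans.
- About 50 sites, so m = 800 / 50 = 16 evaluable patients per site if sites are equal.

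The 95% level comes from Statistical plans; the sample-size paragraph does not state one.

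**Step 1: reproduce the stated figure.**
Half-width = 1.96 × √(p(1 − p)/n) = 1.96 × √(0.45 × 0.55 / 800) = 3.447%, which rounds to 3.4%. Using n = 1,000 gives 3.08%, and a 90% level with n = 800 gives 2.89%, so neither of those lies behind the figure. The stated number is the independent-patient half-width after dropout.

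**Step 2: allow for sites.**
The design effect is DE = 1 + (m − 1) × ICC = 1 + 15 × ICC. The half-width is 3.447% × √DE, and the effective sample size is 800 / DE. The documents give no ICC, so the values below are assumptions.

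**Step 3: coverage if site is ignored.**
A nominal 95% interval computed as if patients were independent covers 2Φ(1.96/√DE) − 1.

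| Assumed ICC | DE | Half-width | Effective n | Coverage of an unadjusted 95% interval |
|---|---|---|---|---|
| 0 | 1.00 | 3.45% | 800 | 95.0% |
| 0.01 | 1.15 | 3.70% | 696 | 93.2% |
| 0.02 | 1.30 | 3.93% | 615 | 91.4% |
| 0.05 | 1.75 | 4.56% | 457 | 86.2% |
| 0.10 | 2.50 | 5.45% | 320 | 78.5% |

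**Step 4: unequal sites.**
With a coefficient of variation (CV) of site size, DE = 1 + ((1 + CV²) × m − 1) × ICC. For an assumed CV of 0.5 this is 1 + (1.25 × 16 − 1) × ICC = 1 + 19 × ICC. The half-widths become 3.76%, 4.05%, 4.81% and 5.87% for the same four ICCs.

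**Step 5: how little correlation is needed.**
Solving 3.447% × √(1 + 15 × ICC) = 3.5% gives an ICC of about 0.002. The stated figure has almost no slack.

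**The case against.** Several points on the other side are sound.

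- **The interval method is not stated.** A reader might infer that the trial's 95% intervals will be too narrow. The text does not support that. The normal approximation is tied to the planning figure only, and the statistical analysis plan, which is not shown, may already use a site-robust interval. The coverage column therefore describes only an interval computed without allowance for site.
- **The ICC is unknown.** A reader might infer a large loss of precision as fact. At an ICC of 0.01 to 0.02 the half-width rises by only 0.3 to 0.5 points. The larger losses need 0.05 or more, and nothing in the article favours those values. A single standardised pathway, common training from the lead investigator, restriction to tertiary hospitals and extra training for sites below target could all reduce differences between sites. The normokalaemia half of the endpoint is also partly a patient matter.
- **Precision is not the only basis for the sample size.** Feasibility is stated first, so a wider half-width does not remove the case for about 1,000 patients.
- **No decision hangs on the figure.** The study is descriptive, with no threshold or test.
- **The calculation is not a miscalculation.** The figure follows exactly from its inputs; the weakness is the unstated independence assumption.

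These points limit the size and certainty of the problem but do not rescue an unqualified 3.4%. A zero ICC would be needed for that figure to hold, and the design makes it unlikely. Treating the 50 hospitals as fixed strata would avoid the widening, but the Discussion presents the sample as representative of a wider CKD population and claims generalisability within China.

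**Conclusion.** The point holds as a correction to a stated planning figure. The 3.4% is right for 800 independent patients and too favourable under any realistic positive within-site correlation. For an assumed ICC of 0.01 to 0.10 and 50 equal sites of 16 evaluable patients, the expected half-width is about 3.7% to 5.5%, and wider with unequal sites. The loss is modest at the low end and material from about 0.05.

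Under-coverage of the reported interval is conditional on its being computed without allowance for site, which the article does not say. The issue does not undermine the sample size, the endpoint or the conduct of the study. It is worth correcting because the estimate and its interval are the main result, but it is not a fault that should hold up the trial.

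**What to change.** 1. In Sample size estimation, state that 3.4% assumes independent patients, and give the expected precision as about 3.7% to 5.5% for an assumed ICC of 0.01 to 0.10 with about 50 sites.
2. Calculate the 95% interval for the primary endpoint with site as the cluster. A design-based interval for a proportion would do, or GEE with robust variance and a small-sample correction. Confirm that the statistical analysis plan says this, or add it.
3. Report the observed ICC with the primary result.

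The cost is a sentence in the sample-size section, a specified procedure in the analysis plan, a less favourable stated precision and a wider interval. No extra patients or visits are needed.

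Adding patients at the same sites would be an inefficient remedy. Holding the 3.447% half-width with 50 equal sites requires m = (1 − ICC)/(1/16 − ICC) evaluable patients per site. That is about 1,180 enrolled at an ICC of 0.01, 1,440 at 0.02 and 4,750 at 0.05.

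There is time for the change. The primary analysis is set for 48 weeks (336 days) after the last enrolment, which the Trial status section expects by January 24, 2026. That places it in late December 2026 at the expected pace.
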